# Evaluation of the efficacy of an interdialytic “ethanol 40% v/v - enoxaparin 1000 U/mL” lock solution to prevent tunnelled catheter infections in chronic hemodialysis patients: a multi-centre, randomized, single blind, parallel group study

**DOI:** 10.1186/s12882-019-1338-6

**Published:** 2019-04-30

**Keywords:** Tunnelled, Hemodialysis, Catheter, Infection, Ethanol, Low molecular weight heparin, Lock

## Abstract

**Background:**

Tunnelled dialysis catheter (TC) infections are a major health complication and are associated with increased antibiotic consumption, hospital stays, health costs and mortality. Experimental data provide evidence that Ethenox, a mixture of enoxaparine 1000 U/mL in 40% *v*/v ethanol, could be a promising lock solution. The aim of the study is to compare an interdialytic lock solution of Ethenox with reference lock solutions, unfractionated heparin (UFH) or citrate 4% for the prevention of TCI in hemodialysis patients.

**Method:**

This study will monitor a multicentre, prospective, single blind, randomized, controlled, parallel group trial. The main inclusion criteria are patients > 18 years old with end-stage renal disease, treated with chronic hemodialysis/hemodiafiltration three times a week, with incident or prevalent non-impregnated internal jugular TCs inserted for at least 2 weeks and able to give informed consent. Exclusion criteria are TCI in the previous 4 weeks and anti-infective treatment for TCI in the previous 2 weeks. Patients will be randomized to receive either study treatment Ethenox in the intervention group or reference solutions in the control group, unfractionated heparin (UFH) or citrate 4% *w*/*v* according to usual practice. The primary outcome measure will be time to first TCIs assessed by an endpoint adjudication committee blinded to the study arm according to predefined criteria. Patients will receive the study treatment for up to 12 months. Intention-to-treat analysis of the primary endpoint will be performed with a marginal Cox proportional hazard model. Prospective power calculations indicate that the study will have 90% statistical power to detect a clinical significant two-fold increase in median infection-free survival if 200 patients are recruited into each arm over a period of 24 months.

**Discussion:**

Firm evidence of the efficacy of the Ethenox lock in preventing TCI could be of major clinical benefit for patients. The results of this study will allow the development of new guidelines based on a high level of evidence.

**Trial registration:**

ClinicalTrials.gov Identifier: NCT03083184, date of registration March 17 2017 and European Clinical Trials Database Identifier: EudraCT 2016-A00180-51), date of registration July 11 2016.

**Electronic supplementary material:**

The online version of this article (10.1186/s12882-019-1338-6) contains supplementary material, which is available to authorized users.

## Background

Infections are the second cause of death in end-stage renal disease patients treated by hemodialysis. The risk of infection of vascular access is ten times greater in chronic hemodialysis patients with a tunnelled catheter (TC) than in those with an arteriovenous fistula. In patients with TC infection (TCI), bacteremia and secondary septic foci occur in 3 to 44% of cases [1]. In chronic hemodialysis patients, TCI results in antibiotics prescription, frequent hospitalizations, and high health costs, and reduces survival [2, 3]. Thus, the prevention of TCI is a major means of improving the prognosis of hemodialysis patients.

Unfractionated heparin (UFH), is the standard interdialytic lock solution for the prevention of TC thrombosis. However, UFH has no antibiofilm properties and could even promote bacteria development [4]. Antibiotic locks decrease the rate of TCI including TC-related bloodstream infections (TCBSI) and exit-site infection (ESI). The widespread use of antibiotic lock solutions raises concerns about the development of adverse events and the emergence of antimicrobial resistance [5, 6]. Antiseptic locks could help to overcome the problem of acquired antibiotic resistance. Hypertonic citrate lock solutions were initially shown to reduce the risk of TCBSI [7, 8]. However, they lead to increased risk of severe pulmonary embolism and even cardiac arrhythmia due to hypocalcaemia, probably as the result of systemic diffusion of concentrated citrate [9]. Other studies found no significant difference in TCBSI incidence between citrate 4% *w*/*v* and UFH lock [10, 11]. A recent meta-analysis reported that antimicrobial-containing citrate locks but not citrate alone reduce the risk of TCI [12]. The use of taurolidine-citrate 4% w/v locks reduces the rate of TCI but increases that of TC dysfunction and TC removal for occlusion [13]. When taurolidine citrate is combined with UFH twice weekly and urokinase once weekly, TC dysfunction does not increase relative to UFH alone. However, the decrease in TCIs caused by Gram-positive cocci, which are the most prevalent cause of TCI in France, is not significant [14]. Hence, it is necessary to develop alternative lock solutions containing an antithrombotic and an additional non-antibiotic substance with antibiofilm properties.

Ethanol is an inexpensive antiseptic agent with activity against a broad range of bacteria and fungi commonly involved in TCI. It acts by non-specific protein denaturation and thus is less likely to promote antimicrobial resistance. Ethanol concentration ≥ 40% *v*/v is highly effective in eradicating biofilm of *Staphylococcus aureus*, *Staphylococcus epidermidis*, *Pseudomonas aeruginosa*, *Klebsiella pneumoniae* and *Candida albicans* [15–17] whereas 46.7% citrate has no antibiofilm properties [18]. Studies have been performed on the integrity of TCs exposed to ethanol: several showed that prolonged exposure of polyurethane and silicon TCs to ethanol at 60% v/v and 70% v/v does not cause ultra-structural damage (electron microscopy studies) or modify their mechanical properties [19, 20]. Likewise, the risk of releasing substances from silicon [21] and polyurethane [22] TCs, as assessed by mass spectrometry, is low at concentrations of ethanol below 60% *v*/v and not different from that observed with a sodium chloride solution at 0.9%.

The HEALTHY-CATH study [23], involving 49 hemodialysis patients fitted with a TC, is the only randomized open label controlled trial to have assessed the efficacy of an ethanol lock strategy for preventing TCBSIs. In the intervention group a-70% *v*/v ethanol interdialytic lock solution was instilled once a week. The reduction of TCBSI risk in this group was not significantly lower than in the heparin group, a result that could have been due to the insufficient power generated by the small patient sample. More recently, a meta-analysis showed that ethanol lock conferred significant benefit in preventing catheter-related bacteraemia in patients with a TC [24].These results suggest that ethanol lock is effective in reducing the rate of TCBSI.

However, ethanol has no specific anticoagulant effect, and our group has previously reported an increase in the rates of TC dysfunction when a 60% *v*/v ethanol interdialytic lock solution is used [25]. Experimental data provide evidence that a mixture of ethanol and injectable anticoagulant may be a promising lock solution for preventing both TCI and TC dysfunctions. UFH, whatever its concentration, cannot be mixed in 40% v/v ethanol because of precipitation. ERA-EDTA recommends using low molecular weight heparins (LMWHs) for blood circuit anticoagulation during dialysis sessions. Like UFH, LMWHs have no antibiofilm properties. In contrast, they can be mixed in 40% v/v ethanol and among LMWHs enoxaparin has the highest solubility (up to 1300 U/mL). Our group has shown that 40% v/v ethanol - enoxaparin 400 U/mL is stable, compatible with TC materials and possesses antibiofilm and anticoagulant properties in vitro (patent). No clinical studies have previously assessed the efficacy of a combined solution of ethanol and LMWH in preventing TCI in chronic hemodialysis patients.

We assume that an interdialytic lock solution of Ethenox, a mixture of enoxaparin 1000 U/mL in 40% v/v ethanol, can be effectively and safely used to prevent TCI in chronic hemodialysis patients. The reduced concentration of ethanol in Ethenox compared to that in previous published reports and the aspiration of the lock before connection for dialysis will enhance tolerance while the addition of enoxaparin will effectively prevent the risk of TC dysfunction.

## Methods/designs

### Aims

The purpose of ETERNITY is to assess the efficacy of an interdialytic lock solution (Ethenox) as compared with reference lock solutions (UFH 5000 U/mL or Citrate 4% *w*/*v*), for preventing TCIs in chronic hemodialysis patients.

### Ethical considerations and registrations

The study is promoted by the Centre Hospitalier Universitaire de Clermont-Ferrand. It was collaboratively designed by the dialysis unit, the medical intensive care unit and the department of clinical research and public health of the university hospital of Clermont-Ferrand, and Unit 6023 (Clermont-Ferrand, France) of the CNRS (French National Center for Scientific Research). The study complies with the principles of the Helsinki Declaration 2008. The whole protocol has been reviewed and approved by the Comité de Protection des Personnes—Sud-Est VI (no. 2016-AU1269). The investigator will explain the study to the eligible patient and give him/her the information form. Patients will be allowed the time they require to make a decision, after which the investigator will collect two initialed copies of the information form and two signed copies of the written consent form. The study is registered on Clinical Trials (NCT03083184) and on the European Clinical Trials Database (EudraCT 2016-A00180-51).

### Design and setting of the study

ETERNITY is a prospective phase III multi-centre, single blind, randomized, controlled, parallel group study (Fig. 1). It will be carried out in 14 dialysis units in France (Additional file 2). The planned duration of the study will be 36 months. The enrolment period will be 24 months. Patients will receive the study treatment for up to 12 months or until 1 month before the end of the study. To evaluate safety, all the patients included will be followed for adverse events for 4 additional weeks after they have received their last treatment dose in the study (Fig. 2).

**Fig. 1 Fig1:**
[figure not shown]
Schema for the Eternity trial. Enrolled patients will be randomly assigned in a 1:1 ratio either to the intervention group (Ethenox) or to the control group (reference solution: UFH 5000 U/mL or citrate 4% *w*/*v* depending on which solution is generally used). Random allocation will be performed by minimization using a computer algorithm. The study will be performed single blind for the patients and the analysts. The primary outcome will be time to first TCIs assessed by an endpoint adjudication committee blinded from study arm according to predefined criteria

**Fig. 2 Fig2:**
[figure not shown]
Scheme of participation in the study for a patient. TC is the statististical unit and several consecutive TC will be analysed in a same patient from the time the inclusion criteria are fullfilled

### Study population

Eligible patients are adult (≥18 years of age) patients undergoing chronic hemodialysis in the study dialysis centres and treated with hemodialysis/haemodiafiltration via a TC inserted in a jugular vein three times a week for at least 2 weeks.

Exclusion criteria are intended use of the catheter for less than 3 months, intolerance of or hypersensitivity to ethanol, enoxaparin or UFH and citrate, previous history of type II heparin-induced thrombocytopenia, local or systemic antibiotic treatment for prevention or treatment of a TCI in the previous 2 weeks, presence of TCI in the previous 4 weeks, previous history of bacteraemia without a negative blood culture evidence of healing, TC impregnated with anti-infective agents or anticoagulants, pregnancy or risk of pregnancy (i.e. pre-menopausal woman not using a reliable method of contraception) and breastfeeding.

### Endpoints

#### Primary endpoints

The primary outcome will be time to first TCI. In the study, TCI is a composite endpoint defined by the occurrence of at least one of the three following events: definitive TCBSI, probable TCBSI or ESI. TCI diagnosis and its type (definitive or probable TCBSI or ESI) will be assessed by an endpoint adjudication committee (EAC, see Additional file 1) blinded to study arm according to predefined criteria (Tables 1 and 2).

**Table 1 Tab1:** TC infections are defined according to the definitions of the guidelines of the DIALIN^6^ network

*TC exit-site infection*	
• Purulent discharge from the exit-site *Or* • Other local signs: redness or pain at the exit-site or along the subcutaneous tunnel (tunnellitis) *And at least one of the following criteria* - Fever (> 38.2 °C) *Or* - Positive blood culture drawn from one of the two lumens of the TC following aspiration of the lock *Or* - Polymorphonuclear leucocytosis In the absence of criterion for TC-related bloodstream infection

**Table 2 Tab2:** The definition of TCBSI is specified according to K/DOQI 2006 clinical practice guidelines for vascular access^57^ which distinguishes between definitive and probable TCBSI

*Definitive TC- related bloodstream infection*	*Probable TC-related bloodstream infection*
At least one positive blood culture drawn from a peripheral vein or the arterial line up to 48 h after TC removal if performed *And at least one of the following criteria:* Positive quantitative broth culture of TC tip (Brun Buisson technique) > 10^2^ UFC/mL with the same microorganism *Or* Positive culture of the exit-site discharge with the same microorganism *Or* Positive blood culture drawn from one of the lumen of the TC following aspiration of the lock with the same microorganism and with a concentration ratio > 3 or a differential time to positivity > 2 h in relation to the blood culture sampled from the peripheral vein *Or* Resolution of signs of infection within 48 h following TC removal with no other apparent source of sepsis other than the TC	At least one positive blood culture drawn from a peripheral vein or the arterial line for a pathogenic microorganism (*S. aureus, enterobacteriaceae*, *pseudomonas sp., Candida sp*.) *Or* At least two positive blood cultures from a peripheral vein or the arterial line *Or* At least one positive blood culture from a peripheral vein or the arterial line in an immunocompromised patient Up to 48 h after TC removal if performed No other apparent source of sepsis other than the TC

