### Sample size calculation

The working hypothesis of this randomized controlled trial is that Ethenox will double the median time to TCI. On the basis of the data collected in DIALIN, median TC duration use is 6 months [29]. The median survival time without TCI reported in recent clinical trials ranges between 690 and 1150 days. However, to achieve a statistical power of 90% with a risk of type I error of 5%, a total of 400 patients need to be enrolled over a period of 24 months.

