### Statistical analysis

#### General consideration

The statistical unit of the primary analysis and of most secondary analyses will be the TC. When a new TC is inserted in a patient participating in the study, the new TC will be analysed for the occurrence of a TCI or TC dysfunction only from the time when the patient fulfils the eligibility criteria. This will rule out ongoing TCI or early dysfunction of the TC due to poor positioning at the time of insertion or an anatomical abnormality of the patient.

The principal analysis will be performed on the intention-to-treat principle with Stata software (version13, StataCorp, College Station, TX). The tests will be two-sided, with a type I error set at α = 0.05. Quantitative variables will be presented as mean ± SD when normally distributed (assumption of normality studied by Shapiro-Wilk test), and for non-normal distributions as median, quartiles and range. Qualitative variables will be expressed as numbers and associated percentages.

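### Table 2 lets two discordant or unrelated blood cultures, or one culture of any organism in an undefined immunocompromised patient, count as probable TCBSI, so contaminants can become primary events

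*Protocol article*

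**What the plan says.** The primary outcome is time to first TCI, a composite of definitive TCBSI, probable TCBSI and exit-site infection (Protocol article, Primary endpoints). A committee classifies events "blinded to study arm according to predefined criteria", and these criteria are Tables 1 and 2.

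Table 2 gives three alternative routes to probable TCBSI:

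1. one positive culture for a listed pathogen (*S. aureus*, Enterobacteriaceae, *Pseudomonas*, *Candida*);
2. "At least two positive blood cultures from a peripheral vein or the arterial line";
3. "At least one positive blood culture from a peripheral vein or the arterial line in an immunocompromised patient".

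The column closes with two conditions: a limit of 48 h after any catheter removal, and the absence of an apparent source of sepsis other than the catheter.

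The definitive column is stricter. Its three culture-based supporting criteria each require the organism to match, for example "Positive culture of the exit-site discharge with the same microorganism".

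**The concern.** The table guards against contaminants in two places: organism matching for definitive TCBSI, and the pathogen list in the first probable route. Routes 2 and 3 have neither guard. Because route 1 already takes the listed pathogens, routes 2 and 3 mainly add other organisms, including skin commensals, and these are the organisms for which concordance matters most.

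Read literally, a febrile patient with a coagulase-negative staphylococcus in one set and a corynebacterium in another meets route 2. A patient on steroids with a single coagulase-negative staphylococcus may meet route 3, depending on who counts as immunocompromised.

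If contamination arises when blood is drawn and is unrelated to the lock, such events dilute the treatment effect and raise the reported TCBSI incidence. Table 1 also allows an exit-site infection only when no TCBSI criterion is met. A loose probable rule can therefore move events from exit-site infection to TCBSI and blur those two secondary endpoints.

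**Working it through.** **1. The plan's own figure.** The inputs are "Ethenox will double the median time to TCI" (HR 0.50 if times are exponential), 90% power, "The tests will be two-sided, with a type I error set at α = 0.05", and "The median survival time without TCI reported in recent clinical trials ranges between 690 and 1150 days".

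- Events needed, with (1.960 + 1.282)² = 10.51: Freedman 10.51 × (1.5/0.5)² = 94.6, so 95; Schoenfeld 4 × 10.51/(ln 0.5)² = 87.5, so 88.
- Event probability over 365 days at a control median of 690 days, with no losses: control 1 − exp(−0.693 × 365/690) = 0.307; Ethenox 0.168; mean 0.237.
- N = 95/0.237 = 401 (Freedman), against the stated 400. Schoenfeld gives 371.

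The stated size is reproduced, at the shortest quoted median and without censoring at catheter removal.

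**2. Assumed inputs (not in the documents).** Contamination c = 3% per culture set (range 2–5%); n = 3 sets per patient-year (range 3–6); immunocompromised share m = 10–30%. Every patient contributes a full year, and nothing is rejected by the source condition or the committee.

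**3. False events per year at c = 3%, n = 3.**

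- At least one contaminated set: p1 = 1 − 0.97³ = 0.0873.
- At least two: p2 = 3 × 0.03² × 0.97 + 0.03³ = 0.00265. Route 2 alone gives 400 × 0.00265 = 1.1 events.
- Both routes: p = (1 − m) × p2 + m × p1.
  - m = 10%: 0.0111, or 4.4 events in 400.
  - m = 30%: 0.0281, or 11.2 events in 400.

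**4. Effect on the hazard ratio, if contamination is equal in both arms.** Control TCI rate L = ln 2/(690/365.25) = 0.367 per year, or ln 2/(1150/365.25) = 0.220 per year. False rate f = −ln(1 − p). Observed HR = (0.5L + f)/(L + f).

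| Case (c = 3%, n = 3) | f per year | HR, 690 days | HR, 1150 days |
|---|---|---|---|
| Route 2 only | 0.0027 | 0.504 | 0.506 |
| Both, m = 10% | 0.0112 | 0.515 | 0.524 |
| Both, m = 30% | 0.0285 | 0.536 | 0.557 |

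**5. Range.** At the low corner (2%, 3 sets), route 2 gives 0.5 events; both routes with m = 10% give 2.8 events and an HR of 0.51–0.52. At the high corner (5%, 6 sets), route 2 gives 13 events and an HR of 0.54–0.57; both routes with m = 30% give 41 events and an HR of 0.61–0.66.

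**6. Effect on power.** False events make up a share f/(L + f) of control-arm events: 0.0112/(0.367 + 0.0112) = 3% at the mildest of the two-route cases in step 4, and 0.0285/(0.220 + 0.0285) = 11% at the worst. Starting from 88 true events (power 90.2%) and adding the false events, a 5% share gives 94.2 events, HR 0.525 and power 87.8%. A 10% share gives 101.0 events, HR 0.55 and power 85.2%.

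**The case against.** Several points on the other side stand.

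- **Safeguards exist.** The no-other-source condition presupposes sepsis, so a positive bottle alone is not enough. The committee may decline to confirm an event (Conduct to be followed in the event of signs of TCI). Even if the closing conditions govern all three routes, they do not separate a contaminant from infection in a patient with unexplained fever. The 48 h limit restricts sampling after removal, not the interval between two cultures. Blinding does not supply a missing criterion.
- **Adjudication is naturally per episode.** A reader might infer that two contaminants months apart would be combined into one event. Table 2 does not forbid it, but committee review follows signs of infection, so that reading is strained. If sets are drawn in pairs per episode, both are contaminated with probability c² = 0.04–0.25%. At an assumed 1.5–3 episodes a year, that is 400 × 1.5 × 0.0004 = 0.24 to 400 × 3 × 0.0025 = 3 events.
- **The two-culture route hardly moves the result.** Most of the shift comes from the third route and its assumed immunocompromised share.
- **Equal contamination is not shown.** Nurses are not reliably blinded (Blinding) and they look for signs of infection, so sampling could differ by arm. Arterial-line cultures may reflect catheter colonisation, which an ethanol lock could reduce. Either could bias the hazard ratio away from 1.
- **The source is not shown.** Table 2 follows a cited guideline, and the full protocol or committee rules may define these terms. However, the article prints the operational table down to colony counts and time to positivity, so the missing organism match is a feature of a stated rule and not just of condensation.

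**Conclusion.** The point holds as a gap in a stated primary-endpoint rule. Route 2 lacks an organism match and a common episode, and route 3 admits any single organism in an undefined group. Contaminants can therefore be counted as primary events.

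Under the central assumptions (3% per set, 3 sets a year) the size is modest: about 1 false event in 400 patients from route 2, and about 4 to 11 from both routes. A true HR of 0.50 becomes about 0.515–0.557. These figures assume equal contamination in both arms and no rejection by the committee; the documents supply none of the contamination inputs.

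A reader might go further and conclude that contaminants will enter the endpoint and will pull the hazard ratio towards 1. The documents support neither step. They give no contamination rate, and they leave open differences between arms that could bias the estimate in either direction. Larger shifts, such as 35 false events and an HR of 0.60–0.65 at 3% and 3 sets, arise if every dialysis patient is treated as immunocompromised. Nothing in the article says so, although leaving the term undefined does not exclude it.

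**What to change.** Before adjudication starts, in Table 2 and in the committee's rules:

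- reword the second probable route to require at least two positive blood cultures with the same microorganism, from separate draws within the same episode, with a fixed window stated;
- define immunocompromised for the single-culture route;
- add a sensitivity analysis of the primary endpoint that excludes events resting on a single common skin commensal.

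Route 3 is kept in the primary definition because removing lone commensals outright would also lose some true infections. The sensitivity analysis shows how far the result depends on them.

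The cost is a line or two in the endpoint table and committee rules; organism and sampling date should already be on routine culture reports. A few true polymicrobial or widely spaced cases would no longer count. The protection is partial, because two contaminants of the same species in one episode would still qualify. Only endpoint classification changes, not patient care.
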